### Data collection measures/instruments

2.10.

The
tools will be administered to participants at each time point. The investigator has taken permission from the respective authors for using the standardized tools. All the tools/instruments were chosen for their usefulness and appropriateness to fulfil the current study’s objectives. All the standardized instruments have been previously used in health and occupational research. The
tools developed by the investigator have been validated by subject experts. Also, feasibility and pilot tests were done to measure the reliability of all the instruments which are to be used in the study.

Demographic variables to be collected are age, gender, education qualification, marital status, type of family, personal annual income, type of job (full time/part-time), and ward/unit.

GENOS EI Inventory (concise version) will be used to assess the staff nurses’ EI. The tool focuses upon the measurement of the frequency of typicality with which an individual exhibits EI, and has 31 items across seven dimensions of emotional awareness of self and others, emotional management of self and others, emotional expression, and emotional self-control. The items are scored on a five-point Likert scale, from ‘almost never’ to ‘almost always’. The test-re-test reliability score of the tool is 0.9 (
Palmer, Stough, Harmer, & Gignac, 2009).

The
Emotional Labour Scale consists of 15 items with the subscales like duration (1 item), frequency (3 items), intensity (2 items), variety (3 items), surface acting (3 items) and deep acting (3 items). The reliability of the tool is 0.83. Respondents are asked to rate “on an average day at work how frequently” they performed interpersonal behaviours on a 5-point Likert-type response scale (1 = never, 5 = always). The higher the score, the higher the emotional labour (
Brotheridge & Lee, 2002).

The
Self Compassion Scale developed by Kristen Neff (
Neff, 2003) will be used in the current study. The test-re-test reliability score of the scale is 0.92. The scale has 12 items that are scored on a five-point Likert scale from “almost never” to “almost always”. The subscales measure self-kindness, self-judgement, humanity, isolation, and mindfulness. Average self-compassion score of 1-2.5 indicates low self-compassion, 2.5-3.5 indicates moderate, and 3.5-5.0 indicates a high level of self-compassion.

Intrinsic motivation will be measured using the
Intrinsic Motivation Scale (IMS) which is developed by the investigator. The scale is developed based on Self Determination Theory (
Ryan & Deci, 2000), Mc Clelland Motivation Theory (
Pardee, 1990), and Motivation to Care Model (
Moody & Pesut, 2006). The scale’s major components are autonomy, competence, relatedness, knowledge, skills, and inner drive. There are 28 items in the IMS, which has been validated by experts with a Content Validity Index of 0.87 and a Cronbach’s alpha reliability score of 0.91.

The
Perception of nursing care tool is developed by the investigator to assess the patients’ and nurse-in-charges’ perception of nursing care before and after the intervention program. The tool has ten items that are scored on a Likert scale from “strongly agree” to “strongly disagree”. The tool has been validated by experts and translated into Kannada (Local language). The Cronbach’s alpha reliability score and Content Validity Index of the tool is 0.93 and 0.87 respectively.

### Data management

2.11

All the questionnaires are paper-and-pen based. So, the data obtained will be entered manually into Microsoft Excel (version 2306) sheets and SPSS (version 20) and will be stored under a folder with a password. The investigator will rectify the mistake if a participant signs their name or any other identifying information on the questionnaire at the time of data collection. The data will all be stored safely on a secure server for further analysis and reference, and the paper copies will be stored safely for five years after the study’s completion.

### Statistical analysis

2.12

Mean and standard deviation will be used to describe measurement data. Frequencies and percentages will be used to represent count data. Repeated measures ANOVA will be used to analyze the effect of the training program. Chi-square will be used to see if an association between the variables before is after the training program.

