### Study participants

2.4

The staff nurses working in the selected hospital’s general wards, who match the inclusion and exclusion criteria, will be considered as a potential study participant. All the nurses who provide their consent to participate will be considered for recruitment in the study. However, only those who fulfill the inclusion criteria will be included for the final sample. The IESE program will be delivered to all the recruited staff nurses. Also, data about the perception of nursing care will be collected from the patients who are under the direct care of the recruited nurse participants, and from the nurse-in-charges who are supervising the recruited nurses. The program will not be provided to the patients and nurse-in-charges.
Table 1 shows the summary of the inclusion and exclusion criteria of study participants. The confounding factors will be controlled by applying an appropriate research design, communicating clearly with the participants and stakeholders, and by making the duty roster of staff nurses well in advance.

**Table 1. T1:** Summary of inclusion and exclusion criteria.

	Nurse	Nurse-in-charge	Patient
**Inclusion criteria**	Staff nurses working in a selected hospital at Mangalore, Karnataka, India.	Nurse-in-charge working in a selected hospital at Mangalore, Karnataka, India.	Patients who are willing to participate.
	Staff nurses who are willing to participate in the study.	Nurse-in-charge who are willing to participate in the study.	Patients in the age group of 18-60-years.
			Patients who can read Kannada and English.
			Patients who are conscious.
**Exclusion criteria**	Staff nurses with earlier exposure to similar programs.	Nurse-in-charge working in psychiatric units, Out-patient-department, and Intensive Care Units.	Patients with current diagnosis of mental illness.
			Patients who are critically ill.
	Staff nurses working in psychiatric units, Intensive Care Units, and Out-patient Departments.		Patients who are admitted for less than 3 days.

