### Study outcomes

2.8

Table 4 shows the primary and secondary outcomes, including the measurement. The secondary objectives/outcomes will be measured using the validated questionnaires at five time-points.

**Table 4. T4:** Summary of the study outcomes and measures.

Outcomes	Description	Measure
Primary	To develop, validate and implement the structured Integrated Emotional-Self Enhancement Program	The researcher has developed a structured program keeping in mind the work structure and stress the nurses might feel in the work and personal environment. The developed program has been validated by the experts who are specialized from the field of nursing management, psychologists, psychiatrists, emotional intelligence, and human resources.
Secondary 1	To determine the impact of Integrated Emotional-Self Enhancement Program on staff nurses’ emotional intelligence	GENOS Emotional Intelligence Inventory (Concise version) ( Palmer, Stough, Harmer, & Gignac, 2009).
Secondary 2	To determine the impact of Integrated Emotional- Self Enhancement Program on staff nurses’ emotional labor	Emotional Labor Scale ( Brotheridge & Lee, 2002).
Secondary 3	To determine the impact of Integrated Emotional-Self Enhancement Program on staff nurses’ self-compassion	Self-compassion Scale ( Neff, 2003).
Secondary 4	To determine the impact of Integrated Emotional-Self Enhancement Program on staff nurses’ intrinsic motivation	Intrinsic Motivation Assessment Scale (developed by the investigator)
Secondary 5	To examine any change in the patients’ perception of nursing care	Perception of Nursing Care Scale (developed by the investigator)
Secondary 6	To examine any change in the nurse-in-charges’ perception of nursing care.	Perception of Nursing Care Scale (developed by the investigator)

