### Data collection

2.9

Data from the staff nurses, patients, and nurse-in-charges will be collected at baseline and 3-month pre-intervention, and immediately after the intervention, at 3-month, and 6-month follow-up by the investigator. Multiple baselines enable an assessment of whether changes occur after or during an intervention, rather than before or as a result of any extraneous factor (
Dundas, Binder, Hansen, & Stige, 2017). The questionnaires will be completed by the participants on the same day. The investigator will always be present with the participants when they fill in the questionnaire and will provide help to understand the questionnaire’s statements if needed. All the participants will be given a unique code to maintain confidentiality and to make sure that only the participants who have consented to participate complete the questionnaires. The investigator will collect the questionnaires on completion and store them safely in a folder. The investigator has considered an attrition rate of 20% while calculating the sample size, to account for participants who discontinue the intervention or follow-ups. Also, the investigator will maintain an attendance sheet of the participants. Reminders will be sent, and calls will be made to the study participants about upcoming and missed sessions.

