## Strengths and Limitations

7.

One of the major strength of this study is that it has used established theories and models to design the conceptual framework that would guide the study. The investigator has also used established theories and models to design the intervention program which improves the credibility of the study. Another strength of this study is using multiple pre-tests and longitudinal post-test data collection method. This would be helpful in indicating the true impact of the IESE Program. However, a major limitation of the study is that there is no control arm in this quasi-experimental study. The unavailability of similar hospitals in terms of infrastructure, workforce and working schedule did not allow the investigator to select another setting that could work as a control arm. Another limitation could be a higher attrition rate due to the unpredictable nature of any hospital setting. Appropriate measures were taken to control this limitation during the sample size calculation. The investigator will also send reminder e-mails and messages to participants before every follow-up. All limitations can veil the true effect of the program. However, considering the current state of COVID-19 pandemic, where staff nurses and healthcare professionals are scarce in general, and to avoid large gatherings that can put the participants’ health at risk, the investigator believes that the current study design and sample size will suffice the study objectives.

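### The named repeated measures ANOVA tests whether any of five visits differs, so change before training can be reported as a programme effect and the second pre-test does not serve its stated purpose

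*Protocol article*

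**What the plan says.** - **Analysis.** Section 2.12 (Statistical analysis) gives the effect one sentence: "Repeated measures ANOVA will be used to analyze the effect of the training program". It names no contrast, comparison of the pre-tests or trend term. The only other test named is chi-square, for association.
- **Visits.** Section 2.8 (Study outcomes): "The secondary objectives/outcomes will be measured using the validated questionnaires at five time-points". Section 2.9 (Data collection) lists the data as "collected at baseline and 3-month pre-intervention, and immediately after the intervention, at 3-month, and 6-month follow-up by the investigator". That is two pre-tests and three post-tests.
- **Purpose of the second pre-test.** Section 2.9: "Multiple baselines enable an assessment of whether changes occur after or during an intervention, rather than before", or because of some outside factor. Section 7 (Strengths and Limitations) counts the repeated pre-tests as a strength: "This would be helpful in indicating the true impact of the IESE Program".
- **Control of confounding.** Section 2.4 (Study participants): "The confounding factors will be controlled by applying an appropriate research design", together with communication and early duty rosters. Section 7, in contrast: "a major limitation of the study is that there is no control arm in this quasi-experimental study".
- **Labels.** Table 3 puts T0 (baseline) in the first pre-test column and T-1 (3-month) in the second, although the subscript suggests that T-1 is the earlier.

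**The concern.** In a one-group design the time effect of a repeated measures ANOVA tests equality of all visit means. It has no term for training. A shift between the two pre-tests, a steady trend, a re-testing effect or a pandemic effect can each make it significant with no programme effect at all.

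There is no control arm, and the study ran from about January 2021 to May 2022, during the pandemic. The second pre-test is the one design feature that could show change already under way before training. If the effect is judged by the time F test, that feature adds one more level to the factor and does not do the job that sections 2.9 and 7 give it. A significant result would then not tell the reader when the change happened.

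**Working it through.** **Inputs from the protocol (section 2.5).** SD 12.3; difference of interest d = 5; two-sided alpha 0.05; 80 nurses recruited; 20% dropout, so 80 × 0.8 = 64 completers.

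**Assumptions, because the protocol gives no figure.** 12.3 is the SD of a score at one visit; the correlation ρ between any two visits is equal, at 0.3, 0.5 or 0.7. If 12.3 was meant as the SD of a change, the ρ = 0.5 case covers it, since 12.3 × √(2 × 0.5) = 12.3. That five visits enter the ANOVA is inferred from sections 2.8 and 2.9; section 2.12 does not say so.

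**1. The plan's own figure.** (1.96 + 0.84)² × 12.3² / 5² = 47.4, where the protocol prints 50. A paired t calculation gives exactly 50, and 50 / 0.8 = 62.5, so 63. The size was thus derived for a single mean change of 5 points, not for an F test with 4 numerator degrees of freedom.

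**2. Time F test with no programme effect.** Noncentral F, df 4 and 4 × 63 = 252, with λ = n Σ(μ − mean)² / [SD²(1 − ρ)]. Visit means are 0, s, s, s, s: a step of s between the two pre-tests and nothing afterwards. For s = 5 the mean is 4 and the sum of squares is 16 + 4 × 1 = 20. At ρ = 0.5, λ = 64 × 20 / (151.29 × 0.5) = 16.9.

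| Step between pre-tests | ρ = 0.3 | ρ = 0.5 | ρ = 0.7 |
|---|---|---|---|
| 5 points | 79.7% | 92.3% | 99.5% |
| 2.5 points | 24.2% | 33.2% | 53.5% |
| 1 point | 7.5% | 8.6% | 11.2% |

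Steady drift behaves in the same way. At ρ = 0.5, 2 points per 3 months (means 0, 2, 2, 4, 6) gives 93%, and 1 point per 3 months (0, 1, 1, 2, 3) gives 34%.

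**3. Pooling the visits does not cure it.** In simulation with n = 80, comparing the mean of the two pre-tests with the mean of the three post-tests still rejects 65% / 80% / 95% of the time for the 5-point pre-test step.

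**4. A planned contrast.** In the same simulation (visit times assumed at 0, 3, 3.5, 6.5 and 9.5 months), first post-test minus last pre-test rejects 4.9% / 4.4% / 5.1% under that step and about 5% to 6% under a drift of 5 points over 9.5 months. It has 86% / 95% / 99.6% power for a true 5-point change at training. Two limits apply. A later post-test absorbs more drift: under that same trend the 3-month visit carries 5 × 3.5 / 9.5 = 1.8 points. And a passing 5-point dip at the last pre-test alone makes the contrast reject 95% of the time at ρ = 0.5. Both are reasons to show the pre-test drift beside it.

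**5. The drift-corrected estimate.** This is the 3-month change after training minus the 3-month change before it, so its weights are 1, −2, 1. At n = 64, ρ = 0.5:

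- simple contrast: SE = 12.3 × √(2 × 0.5 / 64) = 1.54; power for 5 points 89%
- drift-corrected: SE = 12.3 × √(6 × 0.5 / 64) = 2.66, which is √3 times larger; power 46%

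Under the one-off 5-point pre-test step its expected value is 5 − 2 × 5 + 0 = −5. It is then significantly negative 35% / 46% / 67% of the time, although training did nothing.

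**The case against.** The strongest reply is that section 2.12 is a few sentences in a condensed article. It names a family of methods and does not exclude contrasts, which are often left to an analysis plan, and none is shown here. Means and SDs are promised as well; given visit by visit, they would let a reader see a shift before training. This reply stands against the stronger readings that a reader might infer: that the second pre-test is never used, or that drift will be reported as an effect. Both pre-tests would enter the ANOVA as levels, and a false attribution needs some drift to occur. The reply does not remove the point, because the protocol assigns a named test to the effect question and that test does not answer it.

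Second, a 5-point pre-test step is large, since it equals the whole clinically significant difference. That is fair, and is why smaller steps are shown; at 1 point the inflation above 5% is modest.

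Third, it is tempting to allow a programme claim only if the drift-corrected estimate supports it. Step 5 shows why not: the estimate is unbiased only if the pre-test trend continues linearly, and it lacks power for the planned difference.

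Fourth, the protocol openly calls the missing control arm a major limitation. So the weakness is not hidden; the sentence in section 2.4 is simply out of line with section 7. Likewise, every listing of the visits puts baseline first, so the T0 / T-1 matter is one of labelling.

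**Conclusion.** The point holds in this form. The named analysis, read as the time effect over five visits, does not separate change at training from earlier change, so drift or a pre-test shift can be reported as a programme effect. The second pre-test is then not used for the purpose given in sections 2.9 and 7.

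The size depends on how much scores move for other reasons. With no programme effect and 64 nurses, the chance of a significant result runs from about 8% to 11% for a 1-point pre-test step up to 80% to 99.5% for a 5-point step. These rates rest on the assumed correlations and on reading 12.3 as a single-visit SD; the direction does not.

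The documents do not support saying that such drift happened, that contrasts are ruled out, or that a contrast would make the design causal. With one group, an event that coincides with training stays confounded under any analysis.

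**What to change.** 1. **Section 2.12.** Make the effect analysis a planned contrast of one named post-test minus the last pre-test, for example in a mixed model. Report the pre-test drift (last minus first pre-test) with its 95% CI beside it.
2. **Sensitivity analysis only.** Give the drift-corrected estimate, stating that it assumes the pre-test trend continues linearly and has √3 times the standard error. Do not make it a condition for any claim.
3. **Wording of the result.** Describe it as a within-group change.
4. **Table 3.** State T0 and T-1 in months from training, so that the last pre-test and the sign of the drift are unambiguous.
5. **Section 2.4.** Remove the statement that the design controls confounding, in line with section 7.

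The cost is a little more analysis and a more cautious conclusion; no new data are needed. Section 9 (Study status) says that follow-up data collection was completed in May 2022, so the change must be dated and labelled as made after data collection.

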## Abstract

**Background:** Staff nurses face frequent emotional situations in their work environment. The constant contact with suffering patients, and the busy work environment, pose tremendous stress on nurses’ physical and emotional health. The Emotional Intelligence skills of empathy, self-awareness, motivation, self-control, and keeping relationships, can help handle difficult emotions and allow nurses to work in an organized, calm, and professional way.

This study aims to implement and assess the effectiveness of a training program developed by the investigator, tailored to the mental and emotional needs of staff nurses who are working in an organization. The study also aims to observe any significant change, correlation, and association in the staff nurses’ level of emotional intelligence, intrinsic motivation, self-compassion, emotional labor, and nurse-in-charges’ and patients’ perception of nursing care after the program.

**Methods:** A quasi-experimental (one-group) study design was used in this study. The study will involve 80 staff nurses working in a selected hospital in India. The staff nurses will be selected from the hospital’s general wards using convenience sampling. For the current study, a quasi-experimental design will be used. The investigator will deliver a training program, divided into four sessions of two hours each. Data will be collected from the participants at baseline and 3-months pre-intervention; and post-test data will be collected immediately after the intervention, at 3-month, and 6-month follow-up, to observe any significant change in the study variables before and after the intervention.

**Results:** The current study primarily focuses on the vital aspect of developing emotional needs, for promoting a better work-life balance. Research findings from the study will significantly contribute to the evidence based Emotional Intelligence programs for staff nurses, and if proven effective, could be delivered extensively in the hospitals.

**Trial registration:** The study is registered in June 2019 under the Central Trial Registry of India (
CTRI/2019/08/020592).

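### Chi-square is the only named test of association, but the study variables are scale scores, so it requires cutting them into categories and cannot estimate the correlation the abstract aims at

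*Protocol article*

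**What the plan says.** Section 2.12 (Statistical analysis) names two inferential methods. For the effect of the programme: "Repeated measures ANOVA will be used to analyze the effect of the training program". For association: "Chi-square will be used to see if an association between the variables before is after the training program". No other method for association or correlation is named.

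The abstract sets an aim that needs such a method: "The study also aims to observe any significant change, correlation, and association in the staff nurses’ level of emotional intelligence", and it goes on to list intrinsic motivation, self-compassion, emotional labour and perception of care. Section 1.1 (Background) counts the scarcity of work on how the four nurse measures relate to each other among the research gaps it identifies.

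Section 2.10 describes the measures as multi-item scales: 31 items for emotional intelligence, 15 for emotional labour, 12 for self-compassion, 28 for intrinsic motivation and 10 for perception of care. Emotional intelligence: "The items are scored on a five-point Likert scale, from ‘almost never’ to ‘almost always". Emotional labour: "The higher the score, the higher the emotional labour". Only self-compassion has stated bands: "Average self-compassion score of 1-2.5 indicates low self-compassion, 2.5-3.5 indicates moderate, and 3.5-5.0 indicates a high level of self-compassion".

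**The concern.** A chi-square test of association works on a table of counts. To put two scale scores into such a table, each must first be divided into categories. Nurses just above and just below a cut are then treated as different, and nurses far apart within a band as the same. The result depends on cuts that the article does not give for four of the five measures. The test returns a p-value for a table; it gives neither a correlation coefficient nor a confidence interval for one.

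The named test therefore does not fit the stated aim. If it is applied as written, the study has a much smaller chance of detecting a moderate relation between, say, emotional intelligence and self-compassion than the same data would allow. The wording is also garbled, so a reader cannot tell which variables and which time points it covers.

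**Working it through.** **The plan's own figures.** The article states no figure for the association analysis. Its sample size (SD 12.3, difference 5, 80% power) is for a mean change: (1.96 + 0.84)² × 12.3² / 5² = 47.4. The t-based version of that calculation gives the stated 50, and 50/0.8 = 62.5 gives the stated 63. None of this bears on chi-square. The only inputs taken from the article are the planned 80 nurses (section 2.5) and the two-sided 5% level.

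**Assumptions, not in the documents.** The two scores are bivariate normal; the true correlation r lies between 0.2 and 0.5; both scores are split at the median.

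**Correlation test (Fisher z).** Power ≈ Φ(atanh(r) × √(n − 3) − 1.96). At n = 80 and r = 0.3: 0.3095 × √77 = 2.716; 2.716 − 1.96 = 0.756; power 0.775.

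**Chi-square after two median splits.** The 2×2 table has phi = (2/π) × asin(r). At r = 0.3, phi = 0.194. Noncentrality = 80 × 0.194² = 3.01; power on 1 degree of freedom is 0.411. The share of information kept is about (0.194/0.3)² = 0.42.

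| Assumed r | phi | Noncentrality, n = 80 | Power, correlation | Power, chi-square |
|---|---|---|---|---|
| 0.2 | 0.128 | 1.31 | 43% | 21% |
| 0.3 | 0.194 | 3.01 | 78% | 41% |
| 0.4 | 0.262 | 5.49 | 96% | 65% |
| 0.5 | 0.333 | 8.89 | over 99% | 85% |

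A simulation at n = 80 (10,000 runs per setting) agrees: 78% against 39% at r = 0.3, and 96% against 64% at r = 0.4. If 20% drop out, 80 × 0.8 = 64 nurses remain, and the same formulas at r = 0.3 give 68% (0.3095 × √61 = 2.417) against 34% (noncentrality 64 × 0.194² = 2.41).

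**Self-compassion bands.** On 12 items, averages of 2.5 and 3.5 are sums of 12 × 2.5 = 30 and 12 × 3.5 = 42. Both can occur, and each falls in two adjacent bands as printed.

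**If before and after categories were put in one unpaired comparison.** The article does not clearly plan this. It was simulated at n = 80 with a shift of 5, SD 12.3 taken as the SD of each score, a cut at the pre-test mean, and an assumed within-nurse correlation from 0.3 to 0.9. Power was about 51–52% for the unpaired chi-square, 61–95% for McNemar and 86–100% for a paired t-test. With no true change, the unpaired test rejected 2.5% of the time at correlation 0.3, falling to 0.03% at 0.9, against a nominal 5%.

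**The case against.** The strongest defence is that the sentence may mean something ordinary: nurse characteristics against score level, tabulated separately before and after training. Section 2.10 lists gender, education, marital status, family type, job type and ward, most of them categorical already. On that reading each nurse appears once per table. This stands in part. Chi-square is fine where both variables are truly categorical, but crossing a characteristic with a scale score still means cutting the score, and relations among the scores themselves would still lack a suitable method.

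A reader might infer that the plan tests before against after as if the two scores from one nurse were independent, and so yields false positives. The documents do not support this. The sentence can equally mean associations at each time point; the programme effect is assigned to repeated measures ANOVA, a within-nurse method; and even on the hostile reading the unpaired test is conservative. The pairing question does not arise for patients either, since section 2.6 expects different patients at each contact point.

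It is also fair that correlation appears as an aim only in the abstract, not in section 1.2 or Table 4, and that a condensed article may leave a correlation method to a fuller plan. The point here is narrower: the one association test that the article does fix does not suit the variables it describes.

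Finally, r and the median splits are assumptions, and at r = 0.5 chi-square still reaches about 85%. The loss is therefore largest for weak to moderate relations.

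**Conclusion.** The concern holds in limited form. Chi-square, as the only named test of association, does not suit multi-item scale scores and cannot deliver the correlation the abstract promises. With 80 nurses and median splits, power falls from about 78% to about 40% at r = 0.3 and from about 96% to about 64% at r = 0.4. Both the correlations and the splits are assumptions; three-level bands or other cuts would give other figures.

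The planned analysis of mean change is not affected. A fault in the handling of repeated nurses is not established. The overlap of the self-compassion bands at 2.5 and 3.5 is a minor boundary ambiguity. This should be corrected, because it touches a stated aim, but it does not threaten the main analysis of the programme's effect.

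**What to change.** Replace the chi-square sentence in section 2.12 with text that does the following:

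- Estimates Pearson or Spearman correlations, with 95% confidence intervals, between the scores at each visit and between change scores.
- Compares continuous scores across nurse characteristics, or regresses scores on them, without cutting the scores.
- Keeps chi-square for two variables that are both truly categorical.
- States which variables and time points each analysis covers.
- Uses McNemar or a marginal homogeneity test only if before and after categories of the same nurses are put in one comparison.
- Makes the self-compassion bands non-overlapping at 2.5 and 3.5 and uses them for description only.

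The cost is a few lines of text. Section 9 (Study status) reports that follow-up was completed in May 2022, so the change should be made as a dated clarification of the analysis. It uses the data already collected and needs no further nurses.
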